### Outcomes and analysis

Outcome evaluation will be through analysis of routinely-collected GPRD data during a defined study period, while historical information will be used to assess the baseline characteristics of the study patients. Information routinely collected into GPRD for all registered patients includes medical history, use of medicines, hospitalisations and other resource use, smoking history, laboratory tests, letters from specialists or hospitals. GPRD also now links patients in GPRD to the English Hospital Episode Statistics, with detailed information on date, duration and reason for hospitalisation. Availability of data for all registered patients has potential to minimise biases from patient selection/recruitment.

Electronic patient records will be eligible for trial analyses if they describe patients who consult with acute respiratory tract infections, defined using pre-specified Read codes that identify conditions appropriate for study, and are aged 18 to 59 years at the date of the consultation. Pre-intervention GPRD analyses have already been reported [15]. Medical codes have been selected for RTIs including sub-groups of colds, rhinitis and upper respiratory infection; sore throat, pharyngitis and tonsillitis; influenza; laryngitis and tracheitis including croup and epiglottitis; acute sinusitis; otitis media and earache; acute bronchitis; and chest infection and pneumonia. The primary outcome will be the proportion of RTI consultations with antibiotics prescribed over 12 months; secondary outcomes will be age- and sex-specific rates of RTI consultation, age and sex-specific proportion of RTI consultations with antibiotics prescribed, and occurrence of RTI complications. We will use linked Hospital Episode Statistics (HES) data for English practices to evaluate hospitalisation with respiratory illness. Analyses will also be reported separately for each sub-group of RTI codes. In order to provide further insight into safety issues, family practices will be offered the opportunity to notify the study team prospectively of suspected adverse events, in fully anonymised format, during the course of the trial.

Outcomes will be measured through analysis of GPRD electronic prescribing records as described previously [14]. Antimicrobial drugs included will be those in British National Formulary chapter 5.1 excluding anti-tuberculous and anti-leprotic drugs. A maximum of one RTI consultation and antibiotic prescription on the same day will be analysed. Only first consultations within the same episode will be evaluated for the primary outcome, using a 10 day time window. Data for the intervention phase of the trial will be analysed from the intervention start date to 12 months later. Trial analyses will estimate the difference (95% confidence interval) in the proportion of RTI consultations with antibiotics prescribed between intervention and control groups after adjusting for age-group, sex, pre-intervention prescribing proportion. A cluster-level analysis will be implemented using the practice specific proportions as observations, with minimum variance weights to allow for varying numbers of consultations per practice [26].

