### Intervention

Electronic prompts have been developed based on recommended clinical practice guidelines to be activated during consultations for RTI in the selected age range. The electronic prompts promote no antibiotic prescribing, or delayed antibiotic prescribing, instead of the immediate prescription of antibiotics for respiratory tract infections. The prompts specifically incorporate recommendations from the recent NICE guidelines on antibiotic prescribing in respiratory illness [6]. The research also builds on existing work that has identified barriers to reducing antibiotic prescribing [17-19] by designing prompts that briefly address common concerns (e.g. including messages providing evidence regarding likely consequences of delayed prescribing or not prescribing). During consultations with patients presenting with symptoms of respiratory tract infection, primary care professionals will see the prompts which remind them of recommended standards of care in RTI. The prompts will also provide them with supporting information and links to evidence that supports the recommendations, in a format suitable for printing out for patients when appropriate. The decision on whether to follow the treatment suggestions included in the prompt will be at the discretion of the GP. The GP will also be able to terminate display of the prompt at any time. There will be no intervention at control practices. The intervention phase will continue for 12 months at each practice.

The VISION software used by GPRD practices does not presently include any reminders on antibiotic prescribing, so the trial will compare outcomes associated with the new prompts as compared with care with no prompts.

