### Intervention implementation

Prompts will be downloaded automatically through the DXS Point-of-Care system. DXS (UK) Ltd collects data on usage of the information provided. In order to understand utilisation of the intervention, we will analyse fully anonymised practice-level data on usage of the electronic prompts that comprise the intervention.

Initial evaluation has shown that GPs may either begin their record of the consultation by initiating an antibiotic prescription, or by recording a medical code consistent with respiratory tract infection. The prompts are designed to be sufficiently flexible to be activated either by the start of an antibiotic prescription or by the specification of a medical code. 'Antibiotics' are defined as including all drugs in section 5.1 of the British National Formulary with the exception of anti-tuberculous and anti-leprotic drugs. Initially, prompt activation will be by means of medical codes.

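### Antibiotic proportions by RTI code sub-group rest on a code recorded after randomisation, so they could shift through relabelling with no change in prescribing

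*Protocol article*

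**What the plan says.** All places are in Methods/Design of the protocol article.

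- **Eligibility and sub-group** (Outcomes and analysis): records enter the analysis through the code recorded at the consultation, "defined using pre-specified Read codes that identify conditions appropriate for study". The codes fall into eight groups, from colds and upper respiratory infection to chest infection and pneumonia.
- **Measure**: "The primary outcome will be the proportion of RTI consultations with antibiotics prescribed over 12 months". The denominator is coded consultations.
- **Sub-group reporting**: "Analyses will also be reported separately for each sub-group of RTI codes".
- **Data window**: "Data for the intervention phase of the trial will be analysed from the intervention start date to 12 months later".
- **Adjustment**: the between-arm difference is estimated "after adjusting for age-group, sex, pre-intervention prescribing proportion".
- **Population-based outcome**: "secondary outcomes will be age- and sex-specific rates of RTI consultation". No rate of antibiotic-treated RTI consultations per registered patient is listed among the outcomes.
- **Trigger** (Intervention implementation): "Initially, prompt activation will be by means of medical codes". The same section says that practitioners may open the record with either a prescription or a code, and that the prompts can be set to respond to either.
- **Comparator** (Intervention): "There will be no intervention at control practices".

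**The concern.** Randomisation protects a comparison within sub-groups when sub-group membership is fixed before allocation, or at least cannot be changed by it. Neither is assured here. The code is entered during the intervention phase by the person who receives the prompts, and only one arm has prompts. Over 12 months a practitioner who intends to prescribe might come to choose a code that fits an antibiotic better. That consultation would then leave one sub-group's numerator and denominator and join another's.

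The planned adjustment does not deal with this. Age-group, sex and the pre-intervention prescribing proportion describe patients and past prescribing; they do not correct a change in coding after the start.

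What is at stake is the reading of the sub-group table. A pattern such as a fall for upper RTI and none for chest infection could be taken as guidance on where prompts work, and the proportions alone cannot separate that from a change of labels. The Limitations section discusses altered behaviour at control practices but not altered coding at intervention practices.

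**Working it through.** **1. The plan's own yardstick.** The sample size section gives a control proportion of 0.39, 850 eligible consultations per practice, a between-practice coefficient of variation of 0.23, alpha 0.05 (taken as two-sided) and power 0.80. The cluster-level formula is

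c = 1 + (z₁ + z₂)² × [p₀(1−p₀)/n + p₁(1−p₁)/n + k²(p₀² + p₁²)] / (p₀ − p₁)²

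- p₁ = 0.34: 1 + 7.849 × (0.000280 + 0.000264 + 0.014161)/0.0025 = 47.17; the protocol states 47.
- p₁ = 0.33: 32.28; the protocol states 32.

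So the 5% and 6% targets are absolute percentage points for all RTIs combined. They are unaffected by this point and serve below only as a scale.

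**2. Relabelling with prescribing held fixed.** The documents give no sub-group sizes, sub-group prescribing proportions or recoding rate. Assume, per practice, 400 upper-RTI consultations with 120 treated (30%) and 150 chest-infection consultations with 112.5 treated (75%). Move m treated consultations from the first group to the second.

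Upper RTI: (120 − m)/(400 − m). Chest infection: (112.5 + m)/(150 + m). Combined: 232.5/550.

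| Share of treated upper RTI recoded | m | Upper RTI | Change | Chest infection | Change | Combined |
|---|---|---|---|---|---|---|
| 0% | 0 | 30.0% | – | 75.0% | – | 42.3% |
| 5% | 6 | 28.9% | −1.1 | 76.0% | +1.0 | 42.3% |
| 10% | 12 | 27.8% | −2.2 | 76.9% | +1.9 | 42.3% |
| 20% | 24 | 25.5% | −4.5 | 78.5% | +3.5 | 42.3% |

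**3. The same check tied to 850 consultations at 39%.** The split is again assumed: a low-prescribing group with 50% to 80% of consultations at 25% to 33%, and the remainder at 53% to 63%. Here the moved share is a share of all consultations in the low group.

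- Move 5%, all treated: the low group falls by 3.5 to 3.9 points and the high group rises by 2.2 to 6.2. For example, with 510 consultations at 25% and 340 at 60%, moving 25.5 gives (127.5 − 25.5)/(510 − 25.5) = 21.1% and (204 + 25.5)/(340 + 25.5) = 62.8%. The total stays at 331.5/850 = 39.0%. Those 25.5 are 20% of the 127.5 treated consultations in the low group.
- Move 5% with a prescribing proportion midway between the groups: both groups fall, by 0.7 to 2.5 points, again with no change overall. In the same example, at 42.5%, the low group becomes 116.7/484.5 = 24.1% and the high group 214.8/365.5 = 58.8%.

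**4. What population rates would show.** The protocol obtains its 959 consultations per practice as 4,500 × (280 + 146)/2 per 1,000 = 958.5, so 4,500 serves as the denominator. For the 20% row above, per 1,000 registered patients:

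| | Consultations, before → after | Treated consultations, before → after |
|---|---|---|
| Upper RTI | 88.9 → 83.6 | 26.7 → 21.3 |
| Chest infection | 33.3 → 38.7 | 25.0 → 30.3 |
| Both | 122.2 → 122.2 | 51.7 → 51.7 |

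The movement is visible in the parts and cancels in the total. The sub-group treated rates also move, so they expose relabelling but do not correct for it.

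**The case against.** The case on the other side is substantial, and much of it stands.

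- **Order of events.** When a code triggers the prompt, the code precedes the prompt in that consultation. Relabelling then needs later recoding or learning across consultations. This stands as a limit on likelihood. It does not remove the possibility, given 12 months of exposure and a system that can also respond to the start of a prescription.
- **Motive.** Practitioners keep full discretion and can close the prompt. Chest infection is itself among the study's RTI codes, and nothing says that choosing it avoids a prompt. Nothing in the documents shows that relabelling occurs. This stands.
- **The plan may already show code movement.** A reader might infer that the planned consultation rates pool all RTI codes and so cannot reveal movement between groups. The text does not support that: the sentence on sub-groups speaks of analyses in general and follows a list that includes consultation rates, so rates by code group may be intended. The article does not commit to using them as a check on code mix, and they would not correct the proportions.
- **Size.** All inputs to the illustration are assumed, and moving only treated consultations favours a large fall. The 4.5-point figure needs one in five treated upper-RTI consultations recoded, which raises the chest-infection count from 150 to 174 (16%). The 5-point target concerns all RTIs, not a sub-group. All this stands.
- **Left to the analysis plan.** Table layouts may well be. But reporting results by sub-group of the recorded code is a stated choice, and the point concerns how far those results can be interpreted.

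**Conclusion.** The point holds as a limit on interpretation. Sub-group membership is determined after randomisation by a code that the intervention could influence in one arm only, so sub-group antibiotic proportions could move without any change in prescribing. Under the assumed inputs the spurious fall for upper RTI is 1.1 to 4.5 points when 5% to 20% of its treated consultations are recoded. The assumed splits of 850 consultations at 39% give 3.5 to 3.9 points when 5% of the low-prescribing group moves. These figures show sensitivity; they do not estimate a bias.

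Two stronger readings should be resisted. A reader might infer that the primary result is compromised; moves between sub-groups leave the all-RTI proportion exactly as it was in every calculation above. A reader might also infer that the sub-group results are known to be biased; the documents give no evidence that relabelling occurs, nor of its extent.

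**What to change.** Keep the sub-group table and support it as follows.

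1. For each code group, report by arm the RTI consultations and the antibiotic-treated RTI consultations per 1,000 registered patients aged 18 to 59, each adjusted for the practice's pre-intervention value. Give the all-RTI totals of both rates beside them, since moves between groups cancel there.
2. Compare the RTI code mix between arms against the pre-intervention mix.
3. Label the sub-group proportions exploratory and read them alongside these rates. Do not use a non-significant difference in sub-group consultation rates as proof that no relabelling occurred: the comparison may be imprecise, and offsetting moves can leave rates equal. Conversely, a difference in rates may reflect a real effect on consulting.

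The cost is a few extra tabulations and more cautious sub-group statements. No new data collection is needed: the article describes routine records for all registered patients, with historical information. Setting this out before outcome data are seen by arm would make it more credible.

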## Methods/Design

### Objective

To implement a cluster trial in GPRD in a common acute condition. This study aims to test the effectiveness of an electronic record-based intervention at achieving a reduction in antibiotic prescribing at consultations for respiratory illness in patients aged 18 and 59 years in intervention practices as compared with controls.

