### Sample size calculation

The sample size calculation is based on a comparison between the intervention condition, in which the new prompts are present, and usual care, in which no prompts are present. A cluster-level analysis of the practice specific proportions will be implemented. The sample size calculation therefore estimates the number of clusters (practices) required for the study. In a systematic review, quality improvement interventions were associated with reductions in antibiotic prescribing of between 7% and 12% (Ranji et al., 2006). The study therefore aims to detect differences of less than 7%. The selected age-range comprises about 55% of the registered population with about 1,000 registered patients per general practitioner and about 4,500 patients per practice. In data from Gulliford et al. [15], the age-standardised rate of RTI consultations in the 18 to 59 years range was 280 per 1,000 in women and 146 per 1,000 in men in 2006. This suggests there will be about 959 RTI consultations per year, per practice. We observed 1166 consultations in 5,647 person years, [15] consistent with 932 consultations per year per practice. Assuming 10% of consultations may be second visits, there may be 850 eligible consultations per practice. The proportion of consultations with antibiotics prescribed in 2006 was approximately 39% for all RTIs, having declined from 44% in 1997 (unpublished data). We assume that the coefficient of variation of this proportion between practices is 0.23 from Ashworth et al. [14], with alpha = 0.05 and power = 0.8. From Hayes and Bennett [27] equation 4, to detect a 5% difference in the proportion of consultations at which antibiotics are prescribed, 47 practices per group will be required. To detect a 6% difference 32 practices per group will be required. The GPRD includes more than 400 practices and a recent questionnaire of 386 GPRD practices found that 68% (262) were interested in participating in clinical trials. We plan to include 50 practices per group.

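### The first-consultation outcome cannot tell an antibiotic avoided from one postponed within the same 10-day episode

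*Protocol article*

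**What the plan says.** The Objective section sets out to test whether the intervention succeeds in "achieving a reduction in antibiotic prescribing at consultations for respiratory illness in patients aged 18 and 59 years in intervention practices as compared with controls". The Intervention section describes what the prompts do: "The electronic prompts promote no antibiotic prescribing, or delayed antibiotic prescribing, instead of the immediate prescription of antibiotics for respiratory tract infections". For the comparator it says: "There will be no intervention at control practices".

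The Outcomes and analysis section defines the endpoint: "The primary outcome will be the proportion of RTI consultations with antibiotics prescribed over 12 months". It then limits which consultations enter: "Only first consultations within the same episode will be evaluated for the primary outcome, using a 10 day time window". The same paragraph adds: "A maximum of one RTI consultation and antibiotic prescription on the same day will be analysed". For how prescriptions are measured it refers to an earlier cited study.

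The secondary outcomes are RTI consultation rates by age and sex, the proportion of RTI consultations with antibiotics by age and sex, and RTI complications. Hospitalisation is examined in the linked English practices. None of these counts antibiotics per episode or per registered patient, and the article does not say how a delayed prescription is classified.

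**The concern.** The intervention acts on the timing of prescribing as well as on whether an antibiotic is given, but the primary outcome looks only at the first contact.

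Take one illness in each arm. At a control practice the patient is treated on day 0, and the episode scores as treated. At an intervention practice the GP withholds after the prompt, the patient returns on day 4 and an antibiotic is issued. The day-4 visit is not a first consultation, so it is left out and the episode scores as untreated. Each patient received one antibiotic, yet the comparison records a reduction.

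Only one arm is prompted to postpone, so this mechanism differs by arm. Adjustment for pre-intervention prescribing cannot remove an effect that begins with the prompts. What is at stake is the main claim: whether a positive result means fewer antibiotics, or partly the same antibiotics a few days later.

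**Working it through.** **1. The plan's own figure.** Inputs from the Sample size calculation section: control proportion 0.39, difference 0.05 (so 0.34), 850 eligible consultations per practice, between-practice coefficient of variation 0.23, alpha 0.05 (taken as two-sided), power 0.80.

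Practices per group = (1.960 + 0.842)² × [p0(1−p0)/m + p1(1−p1)/m + k²(p0² + p1²)] / (p0 − p1)²

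- Within-practice term: (0.2379 + 0.2244)/850 = 0.00054
- Between-practice term: 0.0529 × (0.1521 + 0.1156) = 0.01416
- Result: 7.849 × 0.01470 / 0.0025 = 46.2, which rounds up to 47 as stated

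For 6 points the same formula gives 31.3, hence 32 as stated. (The variant that adds one cluster gives 48 and 33.) The sample size arithmetic is not at issue. With 50 practices per group, power for a measured 5-point difference is about 82%.

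**2. Relation between measured and episode-level difference.** Let D be the fall in the first-consultation proportion and f the share of shifted patients who receive an antibiotic later in the window. Assume that all other patients have the same later prescribing in both arms, so that they cancel. Then:

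episode-level difference = D × (1 − f)

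**3. A value of f from the protocol's own input.** The Sample size calculation section says: "Assuming 10% of consultations may be second visits". That is 0.10/0.90 = 0.111 return visits per first visit. Assume that shifted patients return at this average rate, at most once each.

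| Antibiotic issued at the return visit | f | Episode-level difference when D = 5 points | Measured / episode-level |
|---|---|---|---|
| Always | 0.111 | 5 × 0.889 = 4.44 | 1.125 |
| At the 39% average | 0.111 × 0.39 = 0.043 | 5 × 0.957 = 4.78 | 1.045 |

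**4. Larger shares, as assumption only.** With f = 25% the episode-level difference is 5 × 0.75 = 3.75 points, and with f = 50% it is 2.5 points. The first-consultation analysis reads 5 points in every case. At the extreme, moving 12.8% of day-0 prescriptions to a later day of the same episode, with no episode spared an antibiotic, gives 0.39 × 0.128 = 5.0 points, and the analysis would be significant with probability about 0.82. The documents give no rate of postponement from which to choose among these.

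**5. Can the listed secondary outcomes show it?** The first-consultation limit is stated only for the primary outcome, so the secondary proportions might include repeat visits. Even then, an antibiotic postponed to a return visit scores 1 of 2 consultations instead of 1 of 1, which still reads as a fall. A higher consultation rate could hint at more returns but would not show whether they ended in an antibiotic.

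**The case against.** **The outcome matches the target.** The prompts aim to replace immediate prescribing, and the objective speaks of prescribing at consultations. Measuring the decision at the first consultation is coherent, and a numerator of any antibiotic in the window would score a script issued on day 3 like one issued on day 0. This stands. It is a reason to keep the present primary outcome, but not a reason to read it as total prescribing.

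**Same-day linkage.** A reader might infer that only antibiotics issued on the day of the first consultation count. The text does not go that far: the same-day sentence reads as a cap on duplicates, and the measurement method is left to a cited source. The point needs only the first-consultation rule, under which a return visit is dropped. The article gives no rule that carries a later prescription back to the first visit.

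**Direction.** A reader might infer that the bias must favour the intervention. A delayed prescription written and recorded on day 0 would count as prescribed, hide a real change in behaviour and pull towards no difference. The article does not say how such prescriptions are recorded. This stands, and the net direction is open.

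**Scope.** A return after the window starts a new episode and is counted, so the problem is confined to the window.

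**Conclusion.** The point holds as a limit on interpretation. As defined, the primary outcome can record prompt-driven postponement within 10 days as reduction, and nothing listed allows the two to be separated.

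At the protocol's average return rate the effect is modest: about 4.4 to 4.8 points per episode behind a measured 5, an overstatement of roughly 5% to 12%. This assumes that shifted patients return like the average patient and that the 10% of second visits describes returns inside the window, which the article implies but does not state.

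A reader might suppose that 20% to 40% of shifted patients are treated later, which would mean 4 to 3 points and an overstatement of 25% to 67%. Nothing in the documents supports that share. With delayed prescriptions on day 0 working in the opposite direction, the documents establish neither the size nor the sign of the net bias.

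**What to change.** Keep the first-consultation proportion as the primary outcome and add to the plan:

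- A pre-specified key secondary or sensitivity analysis with the 10-day episode as unit, counted as treated if any eligible antibiotic from BNF 5.1 is recorded from day 0 to day 10.
- Re-consultation within 10 days, reported by arm.
- A written rule for delayed prescriptions, applied identically in both arms. The episode-level analysis does not settle this alone, because a delayed script recorded on day 0 counts in both versions.
- A wording rule: claim a reduction in antibiotic prescribing, rather than in first-consultation prescribing, only if the episode-level result agrees. Define agreement beforehand: if the planning inputs carry over, 50 practices per group give about 73% power for a 4.5-point episode-level difference.

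The cost is low. The prescribing records are already in GPRD, so this means a different date condition and a little more analysis. A few antibiotics for unrelated conditions will enter the numerator, with no evident reason to differ by arm. Replacing the primary numerator would cost more: the 39% proportion, the 0.23 coefficient of variation and the baseline covariate all concern the consultation proportion and would need to be re-derived.

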### Practices and allocation

Practices are being recruited through a letter of invitation from GPRD. A record will be maintained of the numbers of practices approached, recruited and analysed. Since data for all practices are collected into GPRD, it will be feasible to compare participating and non-participating practices through analysis of anonymised data in GPRD.

GPRD practices are allocated by minimisation, stratifying for region and list size. Allocation is at KCL to ensure allocation is separated from the process of practice recruitment. Patients will be all registered patients aged 18 to 59 years. There will be no other exclusion criteria, so as to optimise both internal and external validity [16].

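### The stated primary analysis leaves out region and list size, the minimisation factors, so its 95% confidence interval may be conservative to the extent that they predict prescribing beyond baseline

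*Protocol article*

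**What the plan says.** On allocation, the section Practices and allocation states: "GPRD practices are allocated by minimisation, stratifying for region and list size".

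On the analysis, the section Outcomes and analysis gives the estimand, the covariates, the unit and the weights. The estimand: "Trial analyses will estimate the difference (95% confidence interval) in the proportion of RTI consultations with antibiotics prescribed". The covariates, given later in the same sentence for the comparison of the two groups: "after adjusting for age-group, sex, pre-intervention prescribing proportion". The unit is the practice, and the weights reflect each one's number of consultations (the quote stops one word short): "A cluster-level analysis will be implemented using the practice specific proportions as observations, with minimum variance weights to allow for varying numbers of consultations per".

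Region and list size are not in the adjustment list. No other section adds them or says why they are absent. The article also gives no figure for how strongly either factor is related to antibiotic prescribing.

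**The concern.** Minimisation forces the two groups to be alike on region and list size. If those factors are prognostic, the forced balance lowers the true sampling variance of the difference between groups. A regression without them does not know about the balance. It leaves their variation in the residual and reports a standard error larger than the real one, so the interval over-covers and the test rejects too rarely under the null.

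What is at stake is precision that the design may already have secured, and agreement between how practices were allocated and how they are analysed. If the choice of covariates is not settled before outcome data are seen, there is also room to choose between two models afterwards.

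**Working it through.** **1. The plan's sample size, to see whether it is touched.** Inputs from the section Sample size calculation: control proportion 0.39 ("The proportion of consultations with antibiotics prescribed in 2006 was approximately 39% for all RTIs"); between-practice coefficient of variation k = 0.23 ("We assume that the coefficient of variation of this proportion between practices is 0.23"); m = 850 ("there may be 850 eligible consultations per practice"); power 0.80; alpha 0.05, taken as two-sided. The cited cluster-trial formula for proportions is

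c = 1 + (1.96 + 0.8416)² × [p0(1−p0)/m + p1(1−p1)/m + k²(p0² + p1²)] / (p0 − p1)².

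- For 0.39 against 0.34 the bracket is 0.000280 + 0.000264 + 0.0529 × 0.2677 = 0.014705. Then c = 1 + 7.849 × 0.014705 / 0.0025 = 47.17.
- For 0.39 against 0.33, c = 32.28.

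The article states 47 and 32, so its figures reproduce. The formula takes no credit for the minimisation factors or for any covariate, so the present point does not alter it.

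**2. Size of the effect on the interval.** Assumptions not in the article: 12 regions, 3 list-size bands, minimisation with a 0.9 biased coin, and a correlation of 0.70 or 0.85 between a practice's baseline and outcome proportions. Region and list size explain a share R² of the variance left after baseline adjustment. Each scenario has 100 practices and 3,000 runs. The regression is unweighted and omits age-group and sex, a simplification of the planned model. Mean 95% interval widths are in percentage points:

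| R² | Without, r = 0.70 | With, r = 0.70 | Excess without | Coverage without | Without / with, r = 0.85 |
|---|---|---|---|---|---|
| 0 | 5.10 | 5.17 | −1.4% | 0.953 | 3.76 / 3.81 |
| Acting only through baseline | 5.09 | 5.15 | −1.2% | 0.947 | 3.76 / 3.82 |
| 0.05 | 5.11 | 5.04 | 1.4% | 0.953 | 3.77 / 3.73 |
| 0.10 | 5.11 | 4.91 | 4.1% | 0.964 | 3.77 / 3.62 |
| 0.20 | 5.12 | 4.63 | 10.6% | 0.967 | 3.77 / 3.41 |
| 0.30 | 5.11 | 4.33 | 18.0% | 0.979 | 3.77 / 3.19 |

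The Monte Carlo error of a coverage near 0.95 is √(0.95 × 0.05 / 3000) = 0.004. The first three rows are therefore indistinguishable from nominal, and the last three are above it.

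**3. The mechanism.** At R² = 0.20 and r = 0.70 the actual standard deviation of the estimate is almost the same in the two models (1.19 and 1.18 points), because minimisation has already removed the imbalance. What differs is the reported precision (width 5.12 against 4.63).

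**4. Hand check.** Under perfect balance the standard error without the factors exceeds the one with them by 1/√(1 − R²). The price of fitting them is 5.17/5.10 = 1.0137. The ratio 1/(1.0137 × √(1 − R²)) gives 1.012, 1.040, 1.103 and 1.179 at R² = 0.05, 0.10, 0.20 and 0.30, close to the simulated 1.014, 1.041, 1.106 and 1.180. Break-even is at R² = 1 − 1/1.0137² = 0.027, or about 3% of residual variance.

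**5. Second simulation.** A separate run with the same categories, on a standardised outcome, gave mean standard errors without and with the factors of 0.199/0.191, 0.199/0.180 and 0.200/0.169 at R² = 0.10, 0.20 and 0.30. The nominal 5% test without them rejected 4.4%, 3.9% and 2.6% of the time under the null.

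**The case against.** The best defence is that the practice's own baseline proportion is already in the model, and it is the natural carrier of stable differences by region or practice size. If region and list size act only through it, omitting them costs nothing and the interval is about 1% narrower without them. This stands: a reader might infer that the interval is definitely too wide, and the article does not support that, because it does not quantify the factors' additional predictive strength.

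A reader might also infer a definite gain in power. The plan's formula at 50 per group gives z = 0.05 / √(0.014705/49) = 2.886, about 82% power for 5 points. Dividing by a standard error ratio of 0.903 (R² = 0.20) gives about 89%. That mixes two variances: the ratio applies after baseline adjustment, while 2.886 takes no credit for it. Scaling the formula by √(1 − r²) for an assumed baseline-outcome correlation r, the change is 86% to 92% at r = 0.3, 92% to 96% at r = 0.5 and 98% to 99% at r = 0.7. The move from 82% to 89% holds only if baseline prescribing predicts nothing, so it should not be used.

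Validity is not in question either. Any error is on the conservative side.

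Last, this is a condensed article, and a fuller analysis plan might add the factors. That softens the point but does not answer it. The article is not silent on covariates: it names a specific set for the trial analysis, and that set does not match the allocation it describes.

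**Conclusion.** The mismatch is real: allocation is balanced on region and list size, and the stated adjustment set contains neither. Its consequence is conditional. The interval is conservative only so far as the two factors predict prescribing beyond the baseline proportion.

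Over an assumed range of 5% to 30% of residual variance the excess width runs from about 1% to about 18%; below roughly 3%, adjusting costs slightly more than it gains. These sizes rest on assumed region and list-size categories, an assumed random element, and an unweighted version of the planned model. They barely change between baseline correlations of 0.70 and 0.85.

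The risks are unequal: about 1% of width if the factors are included needlessly, against 10% or more if they explain a fifth of the residual variance and are left out. That makes the change worth making, as a matter of precision and of consistency with the design rather than of validity.

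**What to change.** Add region and list size, in the categories used for the minimisation, as fixed covariates in the weighted practice-level regression, alongside age-group, sex and pre-intervention prescribing proportion. Report the model without them as a sensitivity analysis. Fix this before outcome data are examined.

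The cost is one line of analysis wording and no new data, since allocation needed both variables for every practice. With 12 regions and 3 bands it uses 11 + 2 = 13 of about 95 residual degrees of freedom, and fewer if region was grouped more coarsely in the minimisation.
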